## Abstract

**Background:**

Recent findings have suggested that implementing the emerging weight-loss strategy of time-restricted eating (TRE) for 6 weeks can have beneficial effects on the key pathophysiologic determinants of type 2 diabetes (T2DM) – namely, pancreatic beta-cell function and insulin resistance. Given the chronic nature of T2DM and the general challenge of long-term adherence to dietary interventions, a critical question is the durability of such effects. Specifically, we seek to determine whether TRE can improve the metabolic health of patients with T2DM over 1 year.

**Methods:**

In this open-label, parallel-arm, randomized controlled trial, individuals with overweight/obesity and T2DM of <10 years duration will be randomized to either standard lifestyle recommendations or TRE. The TRE protocol will consist of 18 hours of fasting and a 6 hour window of eating (between 2–8 PM) each day. The duration of the intervention will be 52-weeks and participants will undergo metabolic characterization at baseline, 12–24-, 36- and 52-weeks. The primary outcome of pancreatic beta-cell function will be assessed by Insulin Secretion-Sensitivity Index-2 (ISSI-2). Additional metabolic measures will include insulin resistance and glucose homeostasis.

**Discussion:**

TRE may represent an adjunct therapeutic approach for improving the metabolic profile of overweight/obese individuals with T2DM while also providing the capacity for modification of its underlying pathophysiology. This evaluation of the durability of the metabolic effects of TRE on beta-cell function and insulin resistance could thus identify a role for this dietary strategy as a disease-modifying intervention early in the course of T2DM.

**Trial registration:**

clinicaltrials.gov NCT07272460.

## Introduction

### Background and Rationale

The relationship between excess weight and type 2 diabetes (T2DM) is clear with approximately 61% to 74% of T2DM cases directly attributable to obesity [1–3]. Excess weight confers additional morbidity as increased BMI in these patients has been linked to poorer cardiovascular risk profile and higher mortality [4–7]. In this context, nutritional therapies targeting weight loss have been shown to improve glycemic control and, in turn, reduce the need for glucose-lowering medications in patients with T2DM [8–10]. However, studies of lifestyle interventions in T2DM have reflected the challenges of maintaining weight loss and achieving sustained glycemic control using non-pharmacological approaches [11,12]. Indeed, a meta-analysis of eleven such trials came to the conclusion that there was no significant impact on glycemic control after one year [11]. The long-term challenges of lifestyle changes in this patient population likely reflect not only the difficulty of prolonged adherence to lifestyle modification but the progressive natural history of T2DM. The natural history of T2DM is driven by 2 main pathophysiologic defects: (1) target cell resistance to the activity of insulin (insulin resistance) and (2) insufficient secretion of insulin by the pancreatic beta-cells to compensate for this peripheral tissue resistance (beta-cell dysfunction) [13,14]. The chronic nature of T2DM is driven by the progressive worsening of beta-cell dysfunction over time, which itself can be further exacerbated by insulin resistance [15]. While lifestyle interventions that have achieved weight loss have been shown to improve insulin resistance [3,9], their impact on pancreatic beta-cell function is not fully understood. Overall, there is no current anti-diabetic medication or lifestyle intervention that has conclusively been shown to prevent the deterioration of beta-cell function in patients with T2DM [14]. Thus, a fundamental problem in the clinical management of T2DM is the inability of current interventions to prevent the deterioration of beta-cell function that underlies the progressive natural history of this condition [13,14].

A recent lifestyle intervention of interest is time-restricted eating (TRE), which involves limiting food intake to a prescribed window of 4−8 hours [16–20]. Unlike traditional diets, TRE does not require calorie counting or specific food regulations/restrictions yet can achieve weight loss comparable to standard calorie-restrictive approaches [21,22]. Beyond weight reduction, TRE can offer additional metabolic benefits by promoting a shift from glucose utilization via glycogenolysis to lipolysis during prolonged fasting which is a pathway less dependent on insulin [23]. This shift suggests TRE may be a particularly relevant tool in managing conditions characterized by hyperinsulinemia (such as insulin resistance). Given its implications for insulin resistance, the impact of TRE on beta-cell function is of interest. To address this question, we recently conducted a randomized cross-over trial in which 39 overweight/obese participants with early T2DM completed 6 weeks of TRE (20 hours fasting/ 4 hours eating) or standard lifestyle [24]. Compared to standard lifestyle, TRE improved beta-cell function (Insulin Secretion-Sensitivity Index-2 (ISSI-2)), reduced hepatic insulin resistance (Homeostasis Model Assessment of Insulin Resistance (HOMA-IR)), and lowered HbA1c (−0.32 ± 0.48%, p < 0.001) [24]. These improvements were accompanied by reductions of body weight (−3.86 ± 3.1%, p < 0.001), and waist circumference (−3.8 ± 7.5 cm, p = 0.003) [24]. The results of this pilot study suggest that TRE is a pragmatic lifestyle intervention that can improve beta-cell function, insulin resistance, and glucose metabolism in overweight patients with T2DM, accompanied by beneficial effects on adiposity and negligible adverse effects. However, the outstanding question that remains is whether this lifestyle intervention can be sustained over time [25]. We are thus performing an open-label, parallel-arm, randomized controlled trial to determine whether TRE over 52-weeks is associated with improvement in beta-cell function, insulin resistance, and glucose homeostasis as compared to standard lifestyle in overweight/obese individuals with early T2DM.

### Objectives and hypothesis

Our trial has 3 main objectives. Firstly, the primary objective in this study is to evaluate the impact of TRE on beta-cell function in overweight/obese individuals with early T2DM as compared to standard lifestyle recommendations over a 52-week period. Our secondary objective is to evaluate insulin resistance in people implementing TRE in comparison to those who are applying standard lifestyle intervention. Lastly, our tertiary objective is to evaluate the impact of TRE on glucose homeostasis as compared to standard lifestyle intervention. Our hypothesis is that 52 weeks of TRE will yield (i) improvement in pancreatic beta-cell function, (ii) reduction in insulin resistance, and (iii) improvements in glucose homeostasis as compared to standard lifestyle recommendations.

## Methods

### Trial design and study population

This study is an open-label, parallel-arm, randomized controlled trial that will last a total of 52 weeks. A schematic of the study design can be found in Figs 1 and 2. In this trial, participants with overweight/obesity and T2DM will be randomized to either standard lifestyle recommendations or TRE. The inclusion and exclusion criteria for the study population are listed in Table 1. This study has just started recruitment and has estimated completion date of recruitment and follow up (data collection) of 31/July/2029 with completion of data analysis and reporting of results expected for 2030.

**Table 1 pone.0343494.t001:** Inclusion and exclusion criteria.

*Inclusion Criteria*
• Individuals with previously diagnosed BMI ≥ 25 kg/m^2^ and type 2 diabetes within preceding 10 years.
• Age 18–75 years inclusive
• Stable weight over past 12 weeks (less than 5% change in body weight) (self-reported)
• Diabetes treatment consisting of lifestyle only or metformin, dipeptidyl peptidase-4 (DPP-4) inhibitor, and sodium-glucose co-transporter 2 (SGLT2) inhibitors either as monotherapy or in combination.
• Ability to read and understand English
** *Exclusion Criteria* **
• Current diabetes treatment with insulin, glucagon-like peptide-1 receptor agonists, and/or sulfonylureas.
• Use of any other pharmacological treatment for weight loss
• Previous surgical treatment for weight loss such as gastric bypass or gastric band
• Any history of eating disorder
• Currently pregnant or lactating
• Renal dysfunction as evidenced by estimated glomerular filtration rate < 25 ml/min by CKD-EPI Creatinine Equation
• New York Heart Association class II-IV heart failure
• Hepatic disease considered to be clinically significant (includes jaundice, chronic hepatitis, or previous liver transplant) or transaminases > 2.5X the upper limit of normal
• Malignant neoplasm requiring chemotherapy, surgery, radiation or palliative therapy within the previous 5 years (with the exception of basal cell skin cancer)
• Any other factor likely to limit adherence to the study, in the opinion of the investigators
• Concurrent participation in another research study relevant to diabetes and metabolic health

**Fig 1 pone.0343494.g001:**
[figure not shown]
Participant timeline: Schedule of enrollment, interventions, and assessments.

**Fig 2 pone.0343494.g002:**
[figure not shown]
Schematic of study design.

### Randomization and intervention

Participants will be randomized 1:1 to either standard lifestyle recommendations or TRE protocol by random number generator (https://www.graphpad.com/quickcalcs/randomize1.cfm). Following randomization, the research coordinator will provide the participants with a booklet containing instruction on healthy eating as per Diabetes Canada Clinical Practice Guidelines [26,27] as well as answer any questions that arise. Participants will undergo metabolic characterization at weeks 0, 12, 24, 36, and 52. Those randomized to the standard group will be told to follow their normal schedule (e.g., possibly consisting of a 16 hour window for eating and ~8 hours of fasting daily). Individuals in the TRE protocol group will be instructed to only eat during a window of 6 hours (2–8 PM) while fasting for the remainder of the day. During the fasting period, participants will only be able to drink water, tea, and coffee (without any sugar added). Between the study visits, participants will be contacted by the research coordinator (virtual visits by phone) for reinforcement of the study protocol and assessment of safety. For 2 weeks after each study visit, participants will also wear an intermittently scanned continuous glucose monitoring system (isCGM) device (FreeStyle Libre 2) on their arms to monitor glucose levels. They will scan the isCGM at least 3 times a day, including before and after each meal. Participants will be instructed to record the time of each meal consumed during these two weeks using the FreeStyle Libre free app. Lastly, individuals who do not have a smartphone or who do not want to use their smartphone will be given a FreeStyle Libre 2 reader.

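### People who already eat within roughly the 2–8 PM window can enter the trial and have little contrast between arms, because eligibility ignores habitual eating window and the control arm keeps its usual schedule

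*Protocol article*

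**What the plan says.** Under Randomization and intervention, the Protocol article defines the control condition by the participant's own habit: "Those randomized to the standard group will be told to follow their normal schedule". It illustrates that schedule with "e.g., possibly consisting of a 16 hour window for eating and ~8 hours of fasting daily", which is an example and not a requirement. The TRE arm is "instructed to only eat during a window of 6 hours (2–8 PM) while fasting for the remainder of the day". After randomization, "the research coordinator will provide the participants with a booklet containing instruction on healthy eating", with no restriction to one arm, so the timing of eating is the main planned difference, together with whatever phone reinforcement of the protocol adds.

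On who may enter, Trial design and study population states: "The inclusion and exclusion criteria for the study population are listed in Table 1". The entries in Table 1 that come nearest to the point are a weight criterion, "Stable weight over past 12 weeks (less than 5% change in body weight) (self-reported", and a general exclusion, "Any other factor likely to limit adherence to the study, in the opinion of the investigators". No entry concerns usual meal times, the length of the eating window, or current time-restricted eating or intermittent fasting.

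**The concern.** The two provisions combine badly. A person who already eats only from early afternoon to evening meets Table 1. In the standard arm that person is told to carry on and in effect follows the test intervention for 52 weeks. In the TRE arm the same person changes little, and any metabolic benefit of the habit is already in the baseline value. For such participants randomization produces little difference in exposure.

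At stake is the size of the contrast the trial was set up to measure. Each such participant pulls the week-52 differences in ISSI-2, HOMA-IR and time in range towards zero. More participants can restore power, but they do not restore the estimate: the attenuation is the same at any sample size.

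**Working it through.** **Does anything in the article close the gap?**

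- Weight stability: a settled short-window eater has stable weight and passes. Many recent starters could pass too, since the mean weight reduction on TRE in the pilot was 3.86% (Background and Rationale), below the 5% limit.
- Adherence exclusion: it removes people likely to adhere poorly. People who already eat this way would be expected to adhere well.
- Other exclusions: weight-loss drugs, weight-loss surgery and concurrent related research are covered. Current use of the intervention under test is not.
- Meal-time logging: it takes place in the two weeks after each study visit. It is not described as a screening step, and a log started after allocation may already reflect the assigned arm.

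So the gap stands on the text.

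**Inputs.** From Sample size: difference 15, SD 18, alpha 0.05 (taken as two-sided), power 80%, 96 evaluable, hence n = 48 per arm. Assumed: a share p of participants has zero effect, and the SD does not change with p.

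**The plan's own figure.** n per arm = 2 × (18/15)² × (1.960 + 0.842)² = 22.6, so 23 per arm and 46 in total (48 with the t test), not 96. The stated inputs do not reproduce 96. That is a separate matter, but it means dilution has to be shown under two readings:

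- Reading A: the SD of 18 is right. Standard error = 18 × √(2/48) = 3.674. Undiluted power = Φ(15/3.674 − 1.960) = 98%.
- Reading B: 96 participants really give 80% power at 15 points. Implied SD = 15 / [(1.960 + 0.842) × √(2/48)] = 26.2, standard error = 5.354.

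**Dilution.** Expected difference = 15 × (1 − p). Power = Φ(difference / standard error − 1.960). Under reading B, the evaluable N that keeps 80% power is 96/(1 − p)².

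| p (assumed) | Expected difference | Power, A (SD 18) | Power, B (SD 26.2) | N for 80%, B |
|---|---|---|---|---|
| 0% | 15.0 | 98% | 80% | 96 |
| 5% | 14.25 | 97% | 76% | 107 |
| 10% | 13.5 | 96% | 71% | 119 |
| 20% | 12.0 | 90% | 61% | 150 |
| 30% | 10.5 | 81% | 50% | 196 |

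Under reading A, power stays at or above 80% until p is about 30%. Under reading B there is no reserve.

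**The case against.** The strongest reply is that the harm is hypothetical. The article gives no prevalence of short-window eating. Its only hint about usual habits is the 16-hour example, which points away from the problem. Social media is one of three recruitment routes, so nothing shows that the trial will draw people already practising TRE. All of this stands, and p can only be an assumption.

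Second, the loss of contrast is narrower than it first looks. A person who skips breakfast and eats from noon to 10 PM, or who takes caloric drinks in the morning, would still change under an 18-hour daily fast with a fixed window and phone reinforcement. Only a habit close to 2–8 PM removes most of the difference, so 15 × (1 − p) is the worst case, not a central estimate. This also stands.

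Third, a usual-schedule comparator can be defended as pragmatic: the trial then estimates the effect of assigning TRE to patients as they present, and exclusions narrow that population. This is a legitimate aim. But the stated question is whether TRE has lasting effects compared with standard lifestyle, and a control participant who already practises TRE does not inform that comparison.

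Fourth, the meal log from week 0 would make the standard arm's windows visible. That helps in describing the problem, but it neither keeps such people out nor gives a clear pre-randomization value.

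**Conclusion.** The gap is real: eligibility admits people whose usual window is already near the study window, and the control instruction leaves them there. The consequence is attenuation of the week-52 differences, to 13.5 points at p = 10% and 12.0 at p = 20% in the worst case. Power is about 96% and 90% on the stated SD, or about 71% and 61% if the design truly sits at 80%. The article does not settle which reading applies.

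Two stronger conclusions are tempting and not supported. A reader might infer that the trial is headed for a false negative. The documents give no value of p, and on the stated inputs power stays at 90% or more up to p = 20%. A reader might also infer that the comparison is biased by imbalance between arms. Randomization balances such people on average, so the effect is dilution and not confounding.

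This is a worthwhile, inexpensive improvement. It does not invalidate the design.

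**What to change.** At the coordinator's existing eligibility contact (Setting and recruitment), ask whether the person currently practises time-restricted eating or intermittent fasting, and what their usual first and last eating times are. Add to Table 1 an exclusion for current practitioners and for those whose usual window is already close to the study window, with a cut-off that the sponsor fixes in advance.

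Keep the pre-randomization window as a baseline variable, for adjustment and for reporting by arm how far eating windows actually separated. Adjustment alone does not recover a lost contrast, so it supplements the exclusion and does not replace it.

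The cost is one or two questions, an eligibility amendment, a few more screen failures and a slightly narrower population. Recruitment has only just begun, so few participants will have entered under the present criteria. Usual eating times before allocation cannot be recovered reliably later.

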### Outcomes

The primary outcome will be beta-cell function at 52-weeks, measured by ISSI-2 [28,29]. The secondary outcomes will be insulin resistance at 52-weeks, measured by HOMA-IR [30], and percentage time in glucose target range at 52-weeks measured by FreeStyle Libre 2 [31]. Additionally, ancillary outcomes of interest will be comparisons between the study arms of the following measures at 52-weeks: (i) further measures of beta-cell function (ΔISR_0–120_/Δgluc_0–120_ × Matsuda index where ISR is the pre-hepatic insulin secretion rate determined by C-peptide deconvolution [32,33], insulinogenic index/HOMA-IR, and fasting pro-insulin/C-peptide ratio [34]), (ii) measures of insulin sensitivity (insulin sensitivity measured by Matsuda index on OGTT [35]), and (iii) anthropometric measures (body weight, body mass index (BMI), and waist circumference). We will also evaluate differences in measures of glucose homeostasis as assessed by isCGM (time above glucose target range (%), time below glucose target range (%), and mean glucose values), by OGTT (fasting glucose, 2-h glucose, area-under-curve of glucose from 0–120 min), and by HbA1c.

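### The sensor scan rule names only meals and sets no maximum interval, so the longest permitted gap between scans depends on the randomised eating schedule

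*Protocol article*

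**What the plan says.** All instructions on sensor use are in the Protocol article under Randomization and intervention. Each visit is followed by two weeks of sensor wear, described thus: "participants will also wear an intermittently scanned continuous glucose monitoring system (isCGM) device (FreeStyle Libre 2) on their arms to monitor glucose levels". The scan rule is: "They will scan the isCGM at least 3 times a day, including before and after each meal". It gives no maximum interval and asks for no scan on waking, at bedtime or during the fast.

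The same section sets the eating schedules. TRE participants are "instructed to only eat during a window of 6 hours (2–8 PM) while fasting for the remainder of the day". Controls keep their usual routine, which the article illustrates as "possibly consisting of a 16 hour window for eating and ~8 hours of fasting daily".

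Under Outcomes, one of the two secondary outcomes is "percentage time in glucose target range at 52-weeks measured by FreeStyle Libre 2". The further sensor measures are "time above glucose target range (%), time below glucose target range (%), and mean glucose values". The article does not say how long the sensor holds readings between scans, or what happens to readings that are not scanned in time.

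**The concern.** The timing of meals is what is randomised. A scan rule anchored to meals makes the spread of scans over the day depend on treatment arm, even when everyone follows the instructions. Three evenly spaced scans would leave gaps of 24/3 = 8 hours. Three or four scans inside a 6-hour window leave one much longer gap.

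If the sensor cannot hold readings over that gap, the two arms' sensor outcomes would be computed from different parts of the 24 hours. The hours at risk are the evening and night, so overnight lows could be missed in the arm that fasts longest. Readings lost this way cannot be recovered at analysis.

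**Working it through.** **Inputs from the Protocol article**
- TRE eating window: 6 h, 2–8 PM (Randomization and intervention). The abstract's Methods paragraph gives the complement: "The TRE protocol will consist of 18 hours of fasting and a 6 hour window of eating".
- Control eating window: 16 h, offered only as a possible example (Randomization and intervention).
- Scan rule: at least three a day, with meals the only times named.

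**Input not in the article**
- Storage span H, the most recent hours the sensor still holds at a scan. This is an assumption, varied from 6 to 18 h and above.

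**Step 1: the longest permitted gap.** Gap = 24 − eating window.
- TRE: 24 − 6 = 18 h, which matches the article's fasting figure.
- Control example: 24 − 16 = 8 h, which also matches.

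Two TRE meals, each scanned before and after, give 2 × 2 = 4 scans. That meets the daily minimum with no scan outside the window.

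**Step 2: hours lost per day.** Loss = max(0, gap − H). The 2 PM scan recovers the H hours before it, so in TRE the lost stretch runs from 8 PM to (2 PM − H). Captured TRE time is H + 6 hours, of which H are fasting.

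| H (assumed) | TRE loss | TRE hours lost | TRE fasting / captured | Control example loss |
|---|---|---|---|---|
| 6 h | 12 h (50%) | 8 PM–8 AM | 6 of 12 h | 2 h (8%) |
| 8 h | 10 h (42%) | 8 PM–6 AM | 8 of 14 h (57%) | 0 |
| 12 h | 6 h (25%) | 8 PM–2 AM | 12 of 18 h (67%) | 0 |
| 16 h | 2 h (8%) | 8 PM–10 PM | 16 of 22 h (73%) | 0 |
| 18 h or more | 0 | none | 18 of 24 h (75%) | 0 |

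**Step 3: a later last scan.** If the final after-meal scan comes after 8 PM, the TRE gap shortens.
- One hour later, the gap is 17 h. TRE loss is 9 h (38%) at H = 8, 5 h (21%) at H = 12 and 1 h (4%) at H = 16.
- Two hours later, the gap is 16 h. TRE loss is 8 h (33%) at H = 8, 4 h (17%) at H = 12 and none at H = 16.

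**Step 4: the direction of bias.** This illustration takes H = 8 and assumed values, with f the time in range during fasting hours and e that during the eating window. True value = (18f + 6e)/24. Observed value = (8f + 6e)/14.
- f = 80%, e = 60%: true 75.0%, observed 71.4%, a bias of −3.6 points.
- f = 50%, e = 70%: true 55.0%, observed 58.6%, a bias of +3.6 points.
- f = e = 70%: no bias.

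The illustration treats all fasting hours alike. In practice the sign depends on how the lost evening and night hours compare with the hours kept.

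**The case against.** - **The mechanism is not in the document.** The article neither gives a storage span nor says that unscanned readings are lost, and at 18 h or more nothing is lost. This stands, so the size can be given only as a range. The sponsor can look up the span, and the remedy works whatever its value.
- **The rule sets a floor.** It asks for a minimum number of scans and includes meals among the times; it does not confine scans to meals. This stands: 18 h is a worst case that the wording permits, not a gap that it prescribes.
- **The control figure is an illustration.** Controls keep their usual routine, so the 8 h is not fixed. This stands too, but the permitted gaps still differ between arms whenever the usual eating window is longer than 6 h.
- **Scan instructions belong in a participant sheet or the full protocol.** That may be true of fuller detail. But the article does state a rule, and that rule ties scanning to the randomised factor. The point concerns what the rule allows, not what is left out.
- **Other glucose measures do not depend on scanning.** This is correct and limits the importance of the point: HbA1c and the OGTT measures are untouched.

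A reader might also infer that the TRE sensor data would come mostly from eating and post-meal hours, and so would understate the benefit of TRE. The check does not support this. Because the 2 PM scan recovers the late fast, fasting hours make up at least half of the captured time at every span considered. The sign of any bias is open.

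**Conclusion.** The concern holds as a fault in the scan rule with a conditional consequence. As written, the rule lets the longest unscanned gap reach about 18 h in TRE against about 8 h in the control example. Whether data are lost depends on the storage span. The worst case in TRE runs from half of each day at 6 h to nothing at 18 h or more. The article does not support a claim that loss will occur or that it favours one arm.

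Time in range, time above and below range, and mean glucose could be affected. ISSI-2, HOMA-IR, HbA1c and the OGTT outcomes are not.

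One further condition applies. The intervention lasts 52 weeks and the sensor is worn for the two weeks after each visit. The article does not say whether TRE eating continues during the wear that follows week 52. The 52-week secondary outcome is exposed only if it does; the wear periods after the 12-, 24- and 36-week visits fall within the intervention in any case.

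The change is worth making now, because the article reports that recruitment has just started.

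**What to change.** Replace the meal-anchored rule with one clock-based rule that is the same in both arms: for example, scan on waking, at midday, in the evening and at bedtime, with no gap longer than the sensor's storage span. State that span in the protocol. Keep the meal scans as an addition. Report data capture by arm and by time of day alongside the sensor outcomes, so that a reader can see whether coverage was balanced. State also which eating schedule applies during the wear after week 52, so that it is clear what the 52-week sensor outcome measures.

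The cost is an edit to the protocol text and the participant instructions, and one or two extra scans a day for TRE participants during the two-week wear periods.
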